### Randomisation and blinding

Consenting patients will be randomly assigned to intervention or control with 1:1 allocation ratio. Blocked randomisation within strata (median age, gender) will balance potential confounders and keep group sizes equal, and will use a standard permutated block algorithm to protect concealment. A statistician will independently generate random sequences for each stratum and provide this to a clinical trials allocations unit, independent from the research group, who will randomly allocate participants to intervention or control arm post baseline data collection. Patients cannot be blinded to receipt of the intervention but study information will present the equipoise position. The statistician and health economist will be blinded for comparison of the data sets. Once the final results have been obtained, unblinding is permissible to be able to report and disseminate the trial outcomes.

### Outcomes measures

As shown in Fig. 2, outcome assessment at baseline, 6,12, 18 and 24 months: bloods and self-report outcomes will be collected by trial staff. Biometric measures constitute total and high cholesterol lipids, blood pressure, weight in kilogrammes, blood glucose level, height and waist measurement in centimetres, %COHb, blood COppm, which constitute the necessary information to calculate the General CVD Risk Score [31]. The self-report measures comprise quality of life [32] SF-12; psychological distress [33] K-10; the Alcohol Use Disorders Identification Test - consumption [34] AUDIT C-3; the Fagerström Test for Nicotine Dependence [35]; the Medical Outcomes Study Sleep measure [36] MOS Sleep; International Physical Activity Questionnaire [37] IPAQ; Australian dietary guidelines healthy eating quiz [38], Partners in Health [39, 40] PIH; Patient Assessment of Chronic Illness Care [41] PACIC; Singh O’Brien Level of Engagement Scale [42] SOLES. Hospital admissions will be extracted from service records to minimise burden on patients and health care staff.

**Fig. 2 Fig2:**
[figure not shown]
Standard Protocol Items: Recommendations for Interventional Trials (SPIRIT) Figure of enrolment, treatment and assessments over time

Key outcomes will involve assessing change at 6, 12, 18 and 24 months for the following measures:Absolute CVD risk will be measured using the General CVD Risk Score [31]. This measure applies from age 30 years and includes gender, age, systolic blood pressure, smoking in last week (Y/N), diabetes (Y/N), hypertensive medication (Y/N), and either total and HDL cholesterol or body mass index (Aim 1, Hypothesis 1).Health-related quality of life will be measured by the SF-12 [32], a validated and commonly used instrument, producing summary scores for mental health and physical health components. The Australian SF-6D scoring algorithm developed by [name] and colleagues will be applied to generate utilities and calculate quality adjusted life years [43], (Aim 1, Hypotheses 2 and 3).

### Statistical analysis

Data analyses will be undertaken using an *intention-to-treat* methodology, adhering to CONSORT guidelines. However, where necessary, analyses will also adopt a *per protocol* approach. The following processes have informed the sample size calculation for the 10-year CVD risk change score. Our pilot data (*n* = 17) found mean (SD) of 10-year risk to be 16.9% (9.8%). Thus, taking a conservative baseline mean CVD risk score of 10.5% and a proportionate SD of 6% and assuming a correlation of 0.5 between baseline and follow up scores, a sample of 304 (i.e., 152 per group), provides 80% power to detect a relative change of 20% in 10-year CVD risk. This calculation was achieved using Stata’s *sampsi* command. These changes are realistic; other current empirically-designed interventions providing coordination alone [44, 45] or self-management alone [46, 47] have achieved substantial levels of change. If necessary, we will transform non-normal data to meet normality conditions. The present intervention provides *both* coordination and self-management, and also includes management of CVD risk. We will sample a total of 358 participants allowing for an attrition rate of 15%. Linear regression will be employed to analyse primary outcomes, clustering over nurse delivering the intervention to account for possible correlated outcome measures. The dependent variable will be the outcome at follow-up. The independent variables will be the outcome at baseline and group assignment. Diagnostic tests to examine homoscedasticity and normality of residuals will be carried out to ensure model validity. The calculations for each primary outcome assume a Type I error rate of 2.5% to protect the overall Type I error rate of 5%. A three level random effects mixed models, using Stata’s *mixed* command will be used to analyse outcomes at several timepoints. If necessary, time will be reparametrised. Nurse, and individual within nurse, will be entered as random effects to account for correlated measures within an individual. The dependent variable will be the outcome at each timepoint. The independent variables will be group assignment, time and the product term group ‘x’ time. Differences between groups across time will be assessed via the interaction term. All results will be reported with 95% confidence intervals, and a *p*-value of less than 0.05 (two-tailed) will be deemed to be statistically significant. All analyses will use Stata (StataCorp, College Station, Texas).

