### The Flinders Program intervention

The Flinders Program provides both framework and tools to engage the patient and structure self-management assessment, tailored planning, motivational enhancement, disease management, prevention, coordination and outcome measurement. It drives optimal use of current health services. In this trial, intervention-allocated participants will be supported to access existing structures and motivational processes including smoking cessation programs; clinical control of triglycerides and diabetes; one-on-one and group components of weight reduction programs; and, where applicable, initiation and adherence with BP-lowering and lipid medications.

Once training has been undertaken, any clinician can deliver the program; however, in the trial’s instance, mental health nurses will facilitate the intervention. Further, while the Flinders Program can be delivered face-to-face, it can also be provided by phone and/or electronically, according to patients’ needs. A web version of the program allows patients and trial nurses to develop the care plan either face-to-face or via the web. This permits communication in real time, or asynchronously via text or email, enabling monitoring and motivational enhancement. In circumstances where participants are randomised into the intervention and subsequently voice issues with continuing to participate in this group, accommodations are made for withdrawal from the intervention program. However, these participants are given the option to continue providing information at the scheduled follow-up data collection points. Details of intervention steps are provided in Table 1.

**Table 1 Tab1:** Summary of intervention schedule and components

Flinders Program component^a^	Planning and action for:	
	Condition management	CVD risk management

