### Practical challenges

The trial will adopt a pragmatic and flexible approach, essential when conducting research in the public mental health care sector. In order to counter potential risks to achieving study goals, including low participation rates [48, 49] we have recruited highly skilled and experienced trial nurses, who previously held roles working first hand with the target population. Further, there is a large population of potential participants for the trial to access. We note from previous studies that recruitment issues are commonplace among populations with severe mental illness, particularly with psychotic features, as they are typically difficult to engage. Studies of this type are vulnerable to power-related problems as ultimately they rely on agreement by the patient to participate in the trial.

Another aspect of the trial is that it will operate within a community health context whereby referral of potential participants will be undertaken by community health staff who will be simultaneously undertaking their day-to-day roles; these tasks may be prioritised above the needs of the trial. To lessen the risk to study referral numbers, trial nurses (who are community health employees) will actively facilitating the referral process by maintaining a close relationship with consultant psychiatrists, clinical and care co-ordinators. Additionally, for the trial to effectively evaluate the self-management intervention, the protocol requires a series of longer-term follow-up data collection points represented by *both* care-as-usual (control) and the Flinders Program plus care-as-usual (intervention) participants. We have put in place number of strategies to mitigate dropout, including inviting and reviewing participants’ explanations for initial non-participation and subsequent barriers/challenges to involvement reported by current participants, and non-cash honorariums.

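### The primary regression uses one follow-up score, so it cannot draw on a dropout's interim visits; the mixed model that can is not made primary

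*Protocol article*

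**What the plan says.** All of the following is in the protocol article.

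- **Principle** (Statistical analysis): "Data analyses will be undertaken using an *intention-to-treat* methodology, adhering to CONSORT guidelines". A per-protocol approach is added where necessary.
- **Primary model** (same section): "Linear regression will be employed to analyse primary outcomes, clustering over nurse delivering the intervention". Its variables are given as "The dependent variable will be the outcome at follow-up. The independent variables will be the outcome at baseline and group assignment". Each primary outcome is tested at a 2.5% Type I error rate.
- **Second model** (same section): a three-level mixed model with group, time and their product, which "will be used to analyse outcomes at several timepoints". The group comparison is the interaction term. Time may be reparametrised if needed.
- **Visits** (Outcomes measures): "outcome assessment at baseline, 6,12, 18 and 24 months". The regression does not say which visit it analyses. Study design addressing aim 1 describes a 12-month trial with follow-up extended to 24 months.
- **Attrition**: the Statistical analysis section raises 304 to 358 to allow for 15%. Practical challenges says of this population that "they are typically difficult to engage".
- **Leaving**: under The Flinders Program intervention, people may leave the programme but "these participants are given the option to continue providing information at the scheduled follow-up data collection points". Under Trial procedures, a participant whose mental health worsens enough to need admission, or who wishes to stop, is withdrawn from the trial and may later rejoin.
- **Service records** (Outcomes measures): "Hospital admissions will be extracted from service records to minimise burden on patients and health care staff".

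**The concern.** A regression with one follow-up score as the response and baseline as the only outcome covariate has nowhere to put a 6-month score. If the analysed visit is 12 months, a participant seen at baseline and 6 months but not at 12 contributes nothing, unless the missing value is filled in first. The estimate is then unbiased only if, given baseline score and arm, having the 12-month score is unrelated to its value.

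The plan gives reasons to doubt that. Trial withdrawal is tied to mental decline, which bears most directly on the SF-12 and its mental component. The arms also differ in what a participant can leave, since only the intervention arm has a programme to stop. If intervention participants with a poor interim course are more likely to be missing, the regression compares a favourable part of that arm with a less selected control arm and favours the programme. The interim scores that would correct the measured part of this are already collected.

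**Working it through.** **1. The plan's own figures.** Target difference: 0.20 × 10.5 = 2.1 points. SD 6 and correlation 0.5 give a change-score SD of 6 × √(2 × (1 − 0.5)) = 6. With two-sided α = 0.025 and 80% power, n per group = 2 × (2.241 + 0.842)² × 36 / 2.1² ≈ 155.2, rounded up to 156. The plan states 152, for which power is 79.1%. The match is close, and no stated number is wrong. For attrition, 304 / 0.85 = 357.6, so 358, which is exact. The inflation therefore treats the 15% as outside the primary analysis, which fits a regression on people with both scores.

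**2. Assumptions for the bias.** From the plan: SD 6, baseline-to-follow-up correlation 0.5 and 358 / 2 = 179 per arm. Assumed here: the analysed visit is 12 months; correlation 0.5 between baseline and 6 months and 0.7 between 6 and 12 months; no true effect; dropout random in controls; dropout in the intervention arm rising with the 6-month score at log-odds 0.5 to 1.0 per SD. Nurse clustering is ignored.

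**3. Formula.** Let δ be the shift in mean 6-month score among those retained in the intervention arm. The mean 12-month score shifts by 0.7δ and the mean baseline by 0.5δ. Baseline adjustment (slope 0.5) removes 0.5 × 0.5δ, so bias = (0.7 − 0.25)δ = 0.45δ. δ comes from integrating the logistic dropout curve over a normal distribution. The standard error is 6 × √0.75 × √(2/n), where n is the number retained per arm. The false-positive rate is Φ(−2.241 + |bias|/SE) + Φ(−2.241 − |bias|/SE).

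| Attrition | Log-odds per SD | δ (points) | Bias (0.45δ) | SE | False positives |
|---|---|---|---|---|---|
| 15% | 0.5 | −0.44 | −0.20 | 0.596 | 3.3% |
| 15% | 1.0 | −0.80 | −0.36 | 0.596 | 5.3% |
| 25% (assumed) | 0.5 | −0.72 | −0.32 | 0.634 | 4.5% |
| 25% (assumed) | 1.0 | −1.28 | −0.58 | 0.634 | 9.2% |

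Simulation of the same set-up agrees. Bias is −0.21 to −0.37 with 3.2% to 6.2% rejection at 15% attrition, and −0.33 to −0.57 with up to 9.1% at 25%. Using the 6-month score brings bias near zero. So does letting dropout follow the same rule in both arms.

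**4. With a true effect.** Take a true effect of −2.1, half of it present by 6 months, and the same one-arm dropout. The observed-case regression gives −2.31 to −2.43 at 15% attrition and −2.48 to −2.76 at an assumed 30%. Adding the 6-month score returns about −2.07 to −2.12.

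**The case against.** The strongest reply is that the protocol never says complete cases and excludes nobody. Multiple imputation followed by exactly this regression would fit the text, and missing-data handling is commonly left to an analysis plan that is not shown. This stands as far as it goes: the absence of an imputation paragraph is not the point here. The point is the stated choice of estimator. The article fixes a primary model that cannot take interim scores, and assigns the one that can to another purpose.

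Several stronger readings are tempting, and the documents do not support them:

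- *The plan ignores interim visits.* It does not. The mixed model uses every timepoint; the interim scores are absent only from the primary regression.
- *Everyone who leaves is dropped.* People who leave the programme may stay in follow-up, and people withdrawn from the trial may rejoin.
- *The analysis contradicts intention-to-treat.* Analysing people as randomised among those observed is in tension with an unqualified intention-to-treat statement, but is not a direct contradiction.
- *Leaving out admission records is an error.* Admissions are part of neither the CVD score nor the SF-12. At most they could help to predict missing values.

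The bias scenario is also one-sided by design. Nothing in the protocol says that dropout follows the CVD score in one arm and is random in the other; the stated trigger is mental decline. The option to stay in follow-up works against missing data in the intervention arm. The 12-month visit is a reading too: were the analysed visit 6 months, there would be no earlier follow-up score to lose.

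**Conclusion.** The point holds in this limited form. As written, the primary regression gives no weight to a participant with interim scores but no score at the analysed visit, and the already planned model that would keep that participant is not primary. That is a weak choice for a trial that expects 15% attrition and links withdrawal to decline.

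At the planned 15%, under one-arm dropout driven by the 6-month score, the bias in the CVD score is about −0.2 to −0.4 points. That is 0.2/2.1 ≈ 10% to 0.37/2.1 ≈ 18% of the target, in the programme's favour, with false positives of about 3% to 6% against 2.5%. Rates near 9% need an assumed 25% attrition together with the steepest mechanism. If dropout works alike in both arms, bias under no effect is about nil. The SF-12 is exposed to the same mechanism, but its bias is not quantified here. A reader might infer that the trial's result would be invalid; the figures do not support that. They support changing the primary estimator before analysis.

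**What to change.** In the Statistical analysis section:

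1. Name the primary visit. Twelve months fits the 12-month trial described under Study design addressing aim 1.
2. Define the primary estimate as the baseline-adjusted group difference at that visit in all randomised participants.
3. Obtain it in one of two ways, and say which. One is the planned all-visits mixed model with time as categories, reading off the contrast at the primary visit rather than an overall interaction. The other is the stated regression after multiple imputation done separately by arm, using baseline and every attended visit. Admissions from service records may be added as an optional auxiliary variable.
4. Report as sensitivity analyses the regression on observed cases, and a delta-shift analysis that worsens the imputed intervention-arm values until the conclusion changes.

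The cost is wording and a little more analysis in Stata, with no new data and no more participants. The downside is that the primary result then relies on a missing-at-random model; the delta-shift analysis shows how much rests on it.

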**Methods:**

This trial used a rigorous process, including extensive piloting, to develop an intervention that delivers recommended physical health care to reduce CVD risk and improve QoL for people with SMI. Components of this intervention are integrated using the Flinders Program of chronic condition management (CCM) which is a comprehensive psychosocial care planning approach that places the patient at the centre of their care, and focuses on building their self-management capacity within a collaborative approach, therefore providing a recovery-oriented framework. The primary project aim is to evaluate the effectiveness and health economics of the CCM intervention. The main outcome measures examine CVD risk and quality of life. The second aim is to identify essential components, enablers and barriers at patient, clinical and organisational levels for national, sustained implementation of recommended physical health care delivery to people with SMI. Participants will be recruited from a community-based public psychiatric service.

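### Each primary outcome is assigned 2.5% to hold 5% overall, but the stated decision rule is p<0.05 with 95% intervals and makes no exception for the primary outcomes

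*Protocol article*

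**What the plan says.** The abstract of the protocol article names two outcome domains: "The main outcome measures examine CVD risk and quality of life". The hypotheses under Aim 1 list them separately.

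The Statistical analysis section sets the error control: "The calculations for each primary outcome assume a Type I error rate of 2.5% to protect the overall Type I error rate of 5" per cent. This sentence follows the description of the linear regression for the primary outcomes. After the description of the mixed model, the same section closes with a general rule: "All results will be reported with 95% confidence intervals", and a p-value "value of less than 0.05 (two-tailed) will be deemed to be statistically significant". Neither half of that rule sets the primary outcomes apart.

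Two further statements bear on how many tests the 2.5% split has to cover. In Outcomes measures, the SF-12 is described as "producing summary scores for mental health and physical health components", and "Key outcomes will involve assessing change at 6, 12, 18 and 24 months for the following measures". The primary regression is described only by "The dependent variable will be the outcome at follow-up", without a month. The section on the study design for aim 1 describes a trial of 12 months whose follow-up runs on to 24 months.

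**The concern.** Type I error is controlled by the rule that decides significance, not by the level used to choose the sample size. A trial sized at 2.5% per outcome but judged at 5% per outcome has paid for the protection in participants and then does not apply it.

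The conflict matters for any primary p-value between 0.025 and 0.05. One sentence calls such a result significant, and the other implies that it is not. The 95% interval would exclude no effect in exactly these cases, so the reported interval would support the looser reading. The article intends to carry a positive finding into national and international practice, so the rule for calling it positive should not depend on which sentence is followed.

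**Working it through.** **Inputs**, all from the Statistical analysis section: baseline mean risk 10.5%, SD 6%, baseline to follow-up correlation 0.5, relative change 20%, 80% power, 152 per group (304), attrition 15%, 358 recruited.

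**1. Was 2.5% really used for the sample size?**

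- Difference: 0.20 × 10.5 = 2.1 percentage points.
- SD of the change score: 6 × √(2 × (1 − 0.5)) = 6.
- n per group = 2 × [6 × (z for alpha/2 + z for power) / 2.1]².
- Two-sided 2.5%: 2 × [6 × (2.241 + 0.842) / 2.1]² = 155.2, so 156 per group, 312 in total.
- Two-sided 5%: 2 × [6 × (1.960 + 0.842) / 2.1]² = 128.1, so 129 per group, 258 in total.
- Recruitment: 304 / 0.85 = 357.6, so 358, as stated.

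The stated 304 is 2.6% below 312 and far above 258. Put as power at 152 per group: the standard error is 6 × √(2/152) = 0.688, and 2.1 / 0.688 = 3.051. Power is Φ(3.051 − 2.241) = 79.1% at 2.5% and Φ(3.051 − 1.960) = 86.2% at 5%. A baseline-adjusted calculation (SD 6 × √0.75 = 5.20) would need 234 in total at 2.5% and 194 at 5%, so it does not give 304 either. The change-score calculation at two-sided 2.5% is the one that fits the stated 80% power.

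**2. Overall error with two primary outcomes, no true effect on either**

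| Level per outcome | If independent | Upper bound, any correlation |
|---|---|---|
| 0.05 (the stated decision rule) | 1 − 0.95² = 9.75% | 2 × 0.05 = 10% |
| 0.025 (the stated error control) | 1 − 0.975² = 4.94% | 2 × 0.025 = 5% |

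With an assumed correlation of 0.3 between the two outcomes, simulation gives 9.5% and 4.9%, so moderate correlation hardly changes the result.

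**3. Power after the fix**

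At 152 per group and two-sided 2.5%, power for CVD risk is 79.1% on the change score. For the planned regression with baseline as a covariate it is 90.0% at the same correlation of 0.5. Neither figure allows for clustering by nurse. The article shows no sample-size calculation for quality of life, so nothing can be said about its power.

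**4. What the split can cover**

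Two shares of 2.5% use up the 5%. If CVD risk and both SF-12 summary scores were each tested at 2.5%, the overall error would be 1 − 0.975³ = 7.3% if independent (bound 7.5%). This figure is conditional, because the article does not say that both scores are primary.

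**The case against.** The best defence is that a specific rule governs a general one. The 2.5% sentence is about primary outcomes and follows their model. The p<0.05 sentence comes later, after the mixed model, and could be meant for everything else. Reporting 95% intervals beside an adjusted threshold is also a common convention, and an analysis plan that is not shown may state the exception. The intention may well be this, but the wording is not: the interval clause covers all results and the threshold carries no restriction. An analysis plan could follow one sentence only by setting the other aside.

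One could also argue that there is no inflation if success needs both outcomes. But the article splits the error rate between them, and a split is needed only when either outcome can support a claim alone.

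A reader might go further and infer three tests, because the SF-12 has two summary scores; that would give 1 − 0.95³ = 14.3% at 0.05. The article describes what the instrument yields and does not say that both scores are primary. A 2.5% split points to two tests.

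A reader might also infer that success at any of the four follow-ups counts. For three scores at four visits, with assumed correlations of 0.5 to 0.7 over time, that would give 34% to 40% at 0.05. The documents do not support this. The primary regression uses a single follow-up outcome, the repeated measurements go into a mixed model judged by the group-by-time interaction, and nothing says that a result at any visit suffices. Which score and which visit are primary are open details, not stated multiplicity.

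**Conclusion.** The contradiction is explicit and stands on the text of one section. The error control promises 5% overall through 2.5% per primary outcome. The stated decision rule, followed as written, gives up to 10% (9.75% if the two outcomes are independent). The figure assumes two primary tests, no true effect on either, and a claim allowed on either one. The match between 152 per group and a two-sided 2.5% level shows that the 2.5% sentence is not stray wording; this check is possible for CVD risk only.

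The unnamed SF-12 score and time point are secondary to this. They matter because the 2.5% split holds 5% only if there are exactly two tests, but the article gives no ground for quoting an error rate above about 10%.

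**What to change.** - State that each of the two primary outcomes is judged at two-sided p<0.025 and reported with a 97.5% interval.
- Limit the p<0.05 and 95% interval sentence to secondary outcomes and to time points other than the primary one.
- Name one SF-12 summary score and one primary time point, so that the split covers exactly two tests. Twelve months is the natural candidate, given how the design section describes the trial.

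If both SF-12 scores are meant to be primary, the quality-of-life share has to be divided, for example 1.25% each. A Holm procedure over three tests would start at 0.05/3 = 1.67%. There the change-score power for CVD risk at 152 per group is about 74%, so that is not the level for which the trial was sized.

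The cost is a few sentences in the protocol or analysis plan, settled before any comparison between groups is seen. The sample size of 304 evaluable and 358 recruited is unchanged. The only loss is that a primary p-value between 0.025 and 0.05 no longer counts as significant, which is the threshold already used to size the trial for CVD risk.

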**Aim 1**
*Hypotheses:* The delivery of the Flinders Program for SMI will be associated with (1) reduced absolute CVD risk, (2) improved quality of life, and (3) will be cost effective.

**Aim 2:** To explore the requirements for a nationally sustainable translation of recommended physical health management in SMI, using qualitative methods which involves all key stakeholders, to develop a policy framework and a comprehensive implementation training package.

### Study design addressing aim 1

A 12-month 2-group randomised (see Fig. 2) controlled trial, with extended follow-up to 24 months will be conducted to contrast the Flinders Program intervention in addition to usual care, with usual care alone.

Each of the two groups will have approximately 178 participants. The intervention group will receive the Flinders Program, in addition to their usual care. Usual care will be provided by health professional care coordinators in public community mental health clinics. Intervention patients and trial nurses will use Flinders Program care planning tools to identify all CVD risk factors, chronic condition and psychosocial issues, patient-identified priority problems and goals, and consensus about which concerns require action.

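### Where the overall 5% error is kept by fixed 2.5% shares for CVD risk and quality of life, a Holm step-down keeps the same 5% and never has less power; the p < 0.05 sentence must be overridden as well

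*Protocol article*

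**What the plan says.** The abstract of the protocol article (Methods) names two areas of main outcome: "The main outcome measures examine CVD risk and quality of life". The Aim 1 hypotheses expect the programme to be associated with "1) reduced absolute CVD risk, (2) improved quality of life, and (3) will be cost effective".

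The Statistical analysis section sets the error rate: "The calculations for each primary outcome assume a Type I error rate of 2.5% to protect the overall Type I error rate of 5" per cent. That is an equal split between two primary outcomes. No step-down or other sequential procedure is named.

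The same section later says: "All results will be reported with 95% confidence intervals, and a *p*-value of less than 0.05 (two-tailed) will be deemed to be statistically significant".

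The sample-size statement covers CVD risk only: "a sample of 304 (i.e., 152 per group), provides 80% power to detect a relative change of 20% in 10-year CVD risk". No effect size, SD or power is given for quality of life. The Outcomes measures section says that the SF-12 yields two summary scores, mental and physical.

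**The concern.** Under a fixed split, each outcome is held to 2.5% whatever happens on the other. Once one outcome has been shown, its share of the error is no longer needed, but it is not passed on. Holm's procedure passes it on: the smaller p-value is tested at 2.5% and, if that is significant, the larger is tested at 5%. The overall error stays at 5% under any dependence between the outcomes.

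The trial wants to conclude on both CVD risk and quality of life, and the second of these has no power statement. At stake is avoidable loss of power for the second conclusion at the same overall error.

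**Working it through.** **Inputs from the article (Statistical analysis; Randomisation and blinding).** Mean CVD risk 10.5% and SD 6 ("taking a conservative baseline mean CVD risk score of 10.5% and a proportionate SD of 6" per cent); correlation 0.5 ("assuming a correlation of 0.5 between baseline and follow up scores"); 20% relative change, so 0.20 × 10.5 = 2.1 points; 152 per group; 1:1 allocation.

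**Assumed by me.** Quality-of-life effect 0.20, 0.25, 0.30 or 0.35 SD, baseline correlation 0.5, tests independent, no nurse clustering.

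**Step 1. Does 2.5% drive the sample size?** With r = 0.5 the change-score SD is 6 × √(2 × (1 − 0.5)) = 6.
- At two-sided 2.5%: n per group = 2 × [6 × (2.241 + 0.842)/2.1]² = 155.2, so 156 per group and 312 in total. Power at 152 per group is 79.1%.
- At two-sided 5%: 129 per group, 258 in total.

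The stated 304 therefore fits two-sided 2.5% (within 3%) and not 5%. The split is built into the design.

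**Step 2. Power for CVD risk at 152 per group.** The standardised difference is 2.1/6 = 0.35, and power ≈ Φ(m − z).
- Planned baseline-adjusted regression: standard error √(0.75 × 2/152) = 0.0993, m = 0.35/0.0993 = 3.52. Power is 90.0% at 2.5% and 94.1% at 5%.
- Change score: standard error √(2/152) = 0.1147, m = 3.05. Power is 79.1% at 2.5% and 86.2% at 5%.

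**Step 3. Fixed split against Holm.** Write C for CVD risk, Q for quality of life, and P2.5 and P5 for power at each level. For independent tests:
- Q under Holm: P2.5(Q) + P2.5(C) × [P5(Q) − P2.5(Q)]
- Both under the split: P2.5(C) × P2.5(Q)
- Both under Holm: P2.5(C)P5(Q) + P5(C)P2.5(Q) − P2.5(C)P2.5(Q)

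Example at 0.25 SD, baseline-adjusted: m = 0.25/0.0993 = 2.52, P2.5(Q) = 60.8%, P5(Q) = 71.1%. Holm for Q: 0.608 + 0.900 × (0.711 − 0.608) = 70.1%. Both: 0.900 × 0.608 = 54.8% under the split; 0.900 × 0.711 + 0.941 × 0.608 − 0.548 = 66.5% under Holm.

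Baseline-adjusted model:

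| Assumed Q effect (SD) | Q, split | Q, Holm | Gain | Both, split | Both, Holm | Gain |
|---|---|---|---|---|---|---|
| 0.20 | 41.0% | 51.0% | 10.0 | 36.9% | 48.6% | 11.7 |
| 0.25 | 60.8% | 70.1% | 9.2 | 54.8% | 66.5% | 11.7 |
| 0.30 | 78.2% | 84.8% | 6.6 | 70.4% | 80.2% | 9.8 |
| 0.35 | 90.0% | 93.7% | 3.7 | 81.0% | 88.4% | 7.4 |

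The same formulas on the change-score basis give quality-of-life gains of about 8, 9, 8 and 6 points, and gains on both of about 11, 12, 12 and 11 points. In simulation with a test correlation of 0.3, the baseline-adjusted gains are 3 to 10 points for quality of life and 7 to 11 for both.

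**Step 4. If CVD risk has no effect.** The quality-of-life gain is 0.025 × [P5(Q) − P2.5(Q)], which is 0.1 to 0.3 points.

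**Step 5. Overall error (independent tests).**
- Both effects null, split or Holm: 1 − 0.975² = 4.94%.
- Only quality of life null, Holm, CVD power 90%: 0.025 + 0.900 × 0.025 = 4.75%.
- Both tested at 5%, as the last significance sentence would allow: 1 − 0.95² = 9.75%.

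**Step 6. If both SF-12 summaries are primary.** There are then three tests, and Holm's first step is 5%/3 = 1.67% (z = 2.394). On the change-score basis, CVD power at that step is Φ(3.05 − 2.39) ≈ 74%. Reaching 80% needs 2 × [6 × (2.394 + 0.842)/2.1]² = 170.9, so 171 per group against 152.

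**The case against.** **The equal split is valid.** It meets the stated aim of holding 5% overall, and it keeps decisions and simple intervals in agreement. That stands: this is an inefficiency, not an error. But Holm claims everything that the split claims, whatever the effect sizes, so for the tests themselves the choice is not a matter of taste.

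**The split may not be the operating rule.** A reader might infer that quality of life at p = 0.03 beside a clear CVD result fails under this plan. The article does not support that. Its only explicit decision sentence calls p < 0.05 significant for all results, and the 2.5% is attached to the calculations. The power is lost only where the 5% overall error is kept through the split. Nor does the article plan any 97.5% intervals.

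**The size is not a figure from the article.** A reader might take a loss of 7 to 10 points as a property of the plan. It is not. That range needs assumed quality-of-life effects of 0.20 to 0.30 SD and 90% CVD power. At 0.35 SD the gain is about 4 points, and with no CVD effect it is close to zero. The article states 80% power and plans to account for clustering by nurse, which these figures leave out and which would lower all of them.

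**The SAP could settle the procedure.** The choice of procedure often belongs there. Here, however, the article has stated a split, and a second sentence in the same section contradicts it.

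**Conclusion.** The point holds as an efficiency improvement, tied to a contradiction that must be settled at the same time. As written, the section protects 5% only through fixed 2.5% shares and then sets a threshold that does not respect them. If the 5% is honoured through the split, Holm is never less powerful. The gain is about 4 to 10 points for quality of life under the baseline-adjusted model (6 to 9 on the change-score basis) and about 7 to 12 points for showing both outcomes.

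These sizes rest on the article's CVD inputs, on my quality-of-life effects of 0.20 to 0.35 SD with correlation 0.5, and on no nurse clustering. That Holm keeps 5% and rejects at least as much rests on none of these assumptions.

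**What to change.** Before unblinding, in the Statistical analysis section or the SAP:

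1. Name one quality-of-life test as the second primary outcome.
2. Replace the split sentence with: *The two primary outcomes are tested with the Holm procedure at an overall two-sided 5%: the smaller p-value is compared with 2.5% and, if significant, the other with 5%.*
3. State that the p < 0.05 and 95% interval sentence does not govern the decision on the primary outcomes, and report 97.5% intervals for them.
4. Keep the sample-size calculation at 2.5% only while there are two primary tests. If both SF-12 summary scores are primary, Holm's first step is 1.67% and the stated power must be recalculated.

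The cost is a few sentences, with no added patients, visits or data for the two-test family. One small downside: an outcome claimed only at the 5% step may have a 97.5% interval that includes zero. The report must then say that the claim rests on the step-down.
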